**G. Sample size:**

In a study conducted to find the efficacy of preloading combination NRT over standard combination NRT, 6-month sustained abstinence was 47.5% for the intervention group and 27.5% for the control group with a level of significance of 5%, power of 80% in the two-sided test [15.]. This proportion was considered to calculate the sample size for the current study. Eventually, the sample size was derived at 91 in each arm. By considering a loss to follow up of 10% in each arm, the sample size is 100.1 and hence rounded off conveniently to 100 per arm.

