#### Methodology:

**A. Trial Design:** This randomized, controlled, two-armed, single-blinded, superiority trial with 1:1 allocation ratio is designed based on CONSORT 2010 Guidelines. This superiority trial intends to gather further evidence that combination nicotine replacement therapy is more efficient than a fast-acting NRT alone.

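### The 10% loss allowance is computed as 91 × 1.10 and rounded down to 100 per arm, which leaves 90 evaluable rather than the 91 required (a minor arithmetic error)

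*Protocol*

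**What the plan says.** Section G of the Protocol takes its planning rates from a cited study in which "6-month sustained abstinence was 47.5% for the intervention group and 27.5% for the control group", with a 5% significance level and "power of 80% in the two-sided test". From these, "the sample size was derived at 91 in each arm". The loss allowance follows: "By considering a loss to follow up of 10% in each arm, the sample size is 100.1", and the result is "hence rounded off conveniently to 100 per arm". Section A describes a "superiority trial with 1:1 allocation ratio", so the same number applies to both arms.

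Two other sections state a different size. Section C (Recruitment of participants) aims for 490 per arm. Section H (Randomization, blinding, and allocation concealment) specifies 245 blocks of four, which is 980 in total and agrees with 490 per arm.

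**The concern.** A loss allowance should give a number randomised that, after the expected loss, still leaves the number the power calculation requires. Section G multiplies the requirement by one plus the loss rate, where it should divide by one minus the loss rate. It then rounds a minimum requirement down. Both steps lower the number, the second by only 0.1 of a participant. As a result the section's final size does not deliver its own evaluable number under its own loss rate.

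What is at stake is whether the stated calculation is correct, and whether the 80% power holds exactly at the stated size. The trial's ability to detect the planned difference is not in question on this point.

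**Working it through.** **Inputs, from Protocol section G unless noted**
- Abstinence: p1 = 0.475 (intervention), p2 = 0.275 (control); difference 0.20
- Two-sided α = 0.05, z = 1.960; power 80%, z = 0.8416
- Allocation 1:1 (section A)
- Loss to follow-up: 10% per arm
- Stated results: 91, then 100.1, then 100 per arm

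**Step 1: reproduce the 91.** Section G names no formula. The pooled two-proportion formula without continuity correction gives

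n = [1.960·√(2·p̄·(1−p̄)) + 0.8416·√(p1(1−p1) + p2(1−p2))]² / (p1−p2)²

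- p̄ = (0.475 + 0.275)/2 = 0.375
- √(2 × 0.375 × 0.625) = 0.6847
- √(0.475 × 0.525 + 0.275 × 0.725) = 0.6699
- n = 90.79, rounded up to 91

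The starting figure reproduces.

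**Step 2: reproduce the 100.1.** 91 × 1.10 = 100.1. This matches exactly, so the allowance was computed as n × (1 + d) with d = 0.10.

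**Step 3: the allowance that retains 91.** n/(1 − d) = 91/0.90 = 101.1, rounded up to 102 per arm.

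**Step 4: evaluable numbers after a 10% loss**

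| Randomised per arm | Left after 10% loss | At least 91? |
|---|---|---|
| 100 | 90.0 | No |
| 101 | 90.9 | No |
| 102 | 91.8 | Yes |

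Rounding 100.1 up to 101 would not have been enough, so the main fault is the multiplication and not the rounding.

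**Step 5: power by the same pooled formula**

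Power = Φ{[0.20·√n − 1.960 × 0.6847] / 0.6699}

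- n = 90: Φ(0.829) = 79.65%
- n = 91: Φ(0.845) = 80.09%

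The difference is 0.4 percentage points.

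**Step 6: which target size does the budget fit?** The Budget justification gives, per intervention participant, 120 patches at USD 8, 600 gums at USD 0.35 and four cotinine kits at USD 8: 960 + 210 + 32 = USD 1,202. Per control participant, with 90 patches, it is 720 + 210 + 32 = USD 962. One participant in each arm costs USD 2,164 together.
- 100 per arm: 100 × 2,164 = USD 216,400, within the USD 228,400 for materials and supplies
- 490 per arm: 490 × 2,164 = USD 1,060,360, far above it

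The budget is therefore consistent with 100 per arm. At 490 per arm, a 10% loss would leave 441 and no shortfall would arise.

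**The case against.** The strongest objection is that the error is immaterial. The gap is one evaluable participant and two recruits per arm, and 79.65% rounds to 80%. It is also smaller than the spread between standard formulas. The unpooled-variance formula needs 88.05, so 89 per arm, and by that formula 90 per arm gives 80.9%. The arcsine formula gives 90.39. This stands as to weight, and it is why the point is minor. It does not make the arithmetic right: section G sets 91 as its requirement and its own final size and loss rate do not deliver 91.

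A second objection is that the shortfall is conditional. If sections C and H hold, recruitment is 490 per arm and nothing falls short. This also stands. However, section G contains the only derivation in the Protocol and concludes with 100, and the budget fits that figure, so the point is not void.

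A reader might go further and infer that, because the Protocol adopts intention to treat, lost participants will be counted as smokers and the loss of power is larger. The Protocol does not support this. Its Results paragraph states no such rule; when missing data exceed 10% it calls for a pattern-mixture model within mixed-effects logistic regression. The inference also assumes that 47.5% and 27.5% are rates among completers, which section G does not say. If those rates already counted losses as failures, an analysis of all 100 per arm would have 83.7% power and no shortfall.

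**Conclusion.** The point holds as a minor arithmetic error. The allowance in section G should be 91/0.90 = 102 per arm. At the stated 100 per arm, a 10% loss leaves 90 evaluable and 79.7% power, just under the stated 80%.

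This rests on three assumptions: the pooled formula, which is inferred because it reproduces 91; an analysis of the participants who remain after the loss; and 100 per arm as the operative target. No claim is made about power under any other handling of missing outcomes. The result should not be read as showing a materially underpowered trial, nor as a reason to put 102 in place of the 490 per arm and 245 blocks in sections C and H. That conflict is a separate and much larger problem, and this calculation does not settle it.

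**What to change.** Change one sentence in section G, in either of two ways:
- Keep 100 per arm and state that a 10% loss leaves 90 evaluable per arm, with about 79.7% power for 47.5% against 27.5% at two-sided 5%, naming the formula.
- Show the allowance as 91/0.90 = 101.1, rounded up to 102 per arm.

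The first needs no extra recruitment or money; its only downside is a slightly less favourable power figure. The second adds two participants per arm, 204 in total against 200, at about 2 × USD 2,164 = USD 4,328 for patches, gum and cotinine kits.

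Limit this edit to section G. The sponsor should reconcile sections C and H with section G as a separate step, and the number carried forward should come from a correctly computed allowance.

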**H. Randomization, blinding, and allocation concealment:**

When planning a randomized clinical trial, careful caution must be executed in the selection of participants for various arms of the study. Selection and accidental bias may occur when participants are not assigned to study groups with equal probability. Hence, block randomization will be done to obtain the two groups using a computer-generated table. Each block contains four participants in a unique sequence of experimental arm and control arm of 245 blocks. The trial will be single-blinded wherein the participant and the principal investigator will not be aware of the group allocation. Data will be maintained by the senior research fellow. Concealment will be ensured in each participant's group allocation by a sealed envelope with the identity number labeled on the envelope.

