#### B. Study Setting:

The study will be conducted at the National research cardiac surgery Centre, [name], Nur-Sultan, Kazakhstan. This hospital is a tertiary level facility with more than 200 beds. As part of developing the infrastructure for the study, an exclusive tobacco cessation center will be established in a carpet area of 500-600 square feet in the hospital premises. A full-time psychologist shall provide the counseling services and a qualified medical practitioner shall prescribe the nicotine replacement therapy.

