| Nicotine Replacement Therapy for > 20 cigarettes per day                 | 
Nicotine Patch: Preloading for 4 weeks + 12 weeks post quit date
 
 
- 21 mg: 4 weeks before and after quit date
 
- 14 mg: Next 4 weeks
 
- 7 mg: Last 4 weeks
 
 
Nicotine chewing gums 4 mg for 12 weeks post quit date
(12/day on week 1.....1/day on week 12)
 | 
Nicotine Patch: 12 weeks post quit date
 
 
- 21 mg: 4 weeks after quit date
 
- 14 mg: Next 4 weeks
 
- 7 mg: Last 4 weeks
 
 
Nicotine chewing gums 4 mg for 12 weeks post quit date
(12/day on week 1.....1/day on week 12)
 |
| Nicotine Replacement Therapy for < 20 cigarettes per day                 | 
Nicotine Patch: Preloading for 4 weeks + 12 weeks post quit date
 
 
- 21 mg: 4 weeks before and after quit date
 
- 14 mg: Next 4 weeks
 
- 7 mg: Last 4 weeks
 
 
Nicotine chewing gums 2 mg for 12 weeks post quit date
(12/day on week 1.....1/day on week 12)
 | 
Nicotine Patch: 12 weeks post quit date
 
 
- 21 mg: 4 weeks after quit date
 
- 14 mg: Next 4 weeks
 
- 7 mg: Last 4 weeks
 
 
Nicotine chewing gums 2 mg for 12 weeks post quit date
(12/day on week 1.....1/day on week 12)
 |
| CO monitoring, Fagerstorm score, smoking frequency, medication adherence | 0-day, Month- 1, 3, 6, 9, 12                                                                                                                                                                                                                                                                                                                 | 0-day, Month- 1, 3, 6, 9, 12                                                                                                                                                                                                                                                                             |

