## 6. Research environment and training for scientists

The study will involve experienced and young scientists, master and bachelor students of Nazarbayev University. Every member of the project will be involved in the Nicotine replacement therapy program. Scientific importance and the high productivity of the research will be achieved by the integration among the project members.

The project has well-defined objectives which will lead to the implementation of the Afterload nicotine replacement therapy. The equipment's & materials will have to be purchased under the grant funds. An area of 500 square feet will be required at the cardiac surgery research Centre for counselling & nicotine replacement treatment.

This research will compose of two groups, an experimental group & the control group. In both the groups nicotine patches & gums will be given. In the experimental group there will be preloading of nicotine patches. The following equipment will be used for research.

- 1) Portable spirometers
- 2) Carbon monoxide monitor
- 3) Sphygmomanometer
- 4) Weighing scale
- 5) Office furniture and computers

There will be young 3 MPH Graduates recruited in the program. The participation of young scientists in the project will allow them to integrate into the global scientific community.

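### Participants cannot be unaware of their arm when only one arm wears patches before the quit date and no placebo is named; the published fixed block of four adds an avoidable risk of predictable allocation

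*Protocol*

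**What the plan says.** On blinding, section A opens: "This randomized, controlled, two-armed, single-blinded, superiority trial with 1:1 allocation ratio". Section H then says who is meant to be blind: "The trial will be single-blinded wherein the participant and the principal investigator will not be aware of the group allocation".

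On treatment, the experimental column of the therapy table in section J reads: "Nicotine Patch: Preloading for 4 weeks + 12 weeks post quit date". The control column lists patches for the 12 weeks after the quit date and nothing before it. Section 6 repeats the contrast: "In the experimental group there will be preloading of nicotine patches". Item 4 of the budget justification allows 120 patches over 16 weeks per experimental participant and 90 over 12 weeks per control participant. Section D describes the control arm differently, as gum alone.

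On allocation, section H says: "Each block contains four participants in a unique sequence of experimental arm and control arm of 245 blocks". It continues: "Concealment will be ensured in each participant's group allocation by a sealed envelope with the identity number labeled on the envelope". Section B names one hospital: "The study will be conducted at the National research cardiac surgery Centre".

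On the outcome, section E makes a participant non-abstinent when smoking is self-reported and the salivary cotinine test is positive.

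**The concern.** A person who wears a patch for 4 weeks while still smoking knows it, and so does a person who is given none. Without a placebo, the participant blinding stated in section H is a property the design does not have. The medical practitioner who prescribes and the psychologist who counsels (section B) see the same thing.

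Two consequences follow. First, the primary outcome depends partly on what participants say about their own smoking, and so do the number of quit attempts and cigarettes per day in section F. Participants who know their arm may answer differently. The blinding statement is the only protection the protocol offers against this, because it describes no masked outcome assessment. Second, visible regimens at a single site reveal past allocations. With a block size fixed and printed in the protocol, past allocations carry information about the next one, and staff who enrol could let that influence whom they enrol and when. Section H itself gives selection bias as a reason for randomizing in blocks.

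**Working it through.** **Blinding: the sources side by side**

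| Source | Experimental arm before quit date | Control arm before quit date | Placebo patch named? |
|---|---|---|---|
| Section J table | Patch, 4 weeks | None | No |
| Section 6 | Preloading patches | None mentioned | No |
| Budget, item 4 | 120 patches, 16 weeks | 90 patches, 12 weeks | No |
| Section D | Patch and gum | Gum alone, no patch at any time | No |

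The patch counts point the same way. Assuming one patch a day (the protocol gives no daily number), 16 weeks need 16 × 7 = 112 of the 120, leaving 8. Twelve weeks need 12 × 7 = 84 of the 90, leaving 6. Sham wear for 4 weeks would need 4 × 7 = 28 more per control participant, and the control supply has no room for it.

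The arms are thus visibly different under the section J control, and more so under the section D control. The conclusion on participant blinding does not depend on which description is meant.

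**Principal investigator.** Section B gives prescribing and counselling to other staff, and section H gives data maintenance to the senior research fellow, so the principal investigator could remain unaware. Against that, the Declarations have the principal investigator monitor data management, and the text after the Conclusion makes that role the decision maker who reports adverse reactions. No separation from treatment data is described.

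**Outcome.** Taking section E as written:

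| Self-report | Cotinine | Status |
|---|---|---|
| Smoked | Positive | Non-abstinent |
| Smoked | Negative | Not non-abstinent |
| Denies | Positive | Not non-abstinent |
| Denies | Negative | Not non-abstinent |

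A participant who denies smoking is never classed as non-abstinent, whatever the test shows.

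**Predictability of a fixed 2:2 block of four.** There are 4!/(2!·2!) = 6 orders. Suppose the enroller knows where the block starts, has seen every earlier allocation in it, and always guesses the arm with more places left.

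- Position 1: two places left in each arm. P(correct) = 1/2.
- Position 2: two of the three remaining places belong to the other arm. P(correct) = 2/3.
- Position 3: with probability 1/3 the first two match and the third is certain; otherwise one place is left in each arm. P(correct) = 1/3 × 1 + 2/3 × 1/2 = 2/3.
- Position 4: always certain. P(correct) = 1.

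Expected correct guesses: (1/2 + 2/3 + 2/3 + 1)/4 = (17/6)/4 = 70.8%. Certain in advance: (1/3 + 1)/4 = 33.3%.

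In numbers of participants, the 245 blocks give 245 × 4 = 980 = 2 × 490, which matches the target in section C. Of 980, about 327 would be certain and 694 guessed correctly. For the 100 per arm in section G (200 in all), the figures are about 67 and 142.

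For comparison, with block sizes that are also fixed and known:

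| Block size | Certain | Best guess correct |
|---|---|---|
| 4 | 33.3% | 70.8% |
| 6 | 25.0% | 68.3% |
| 8 | 20.0% | 66.6% |

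**The case against.** The strongest reply is that only one statement is clearly contradicted, the one about participants. Much of this stands.

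- A reader might infer that the principal investigator is shown to be unblinded. The documents do not support that. The investigator who explains the information sheet in section C is not said to be the principal investigator, and the hands-on roles belong to others. What can be said is that no separation is described.
- A reader might take 70.8% and 33.3% as the expected effect. They are upper bounds. The protocol does not say who enrols, who opens the envelopes, or whether that person sees what was dispensed. Sealed envelopes are a stated safeguard. They hide the individual assignment but do not stop deduction from earlier ones.
- Fixed blocks of four are a common choice and not in themselves an error. Larger known blocks gain little: 70.8 − 68.3 = 2.5 points for six and 70.8 − 66.6 = 4.2 for eight. The benefit has to come from the sizes being unknown to enrolling staff, and no figure is given here for that.
- A reader might say that self-report is half of the primary outcome. It is not, because section E joins it to cotinine rather than weighing the two. Section D also treats cotinine as the biochemical verification. If either criterion alone were meant to suffice, self-report would decide only among cotinine-negative participants and its influence would be smaller.
- A reader might call the sequence wording impossible: "Each block contains four participants in a unique sequence of experimental arm and control arm". Six orders cannot fill 245 blocks without repetition, but the phrase may only mean that each block has its own generated order. It is loose wording with no effect on results.
- Nor does the protocol hide the difference between arms, which is plain in section J, the budget and section 6.

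The flow diagram and consent pages were not available, so the absence of a placebo rests on the text, the therapy table and the supplies list, which agree.

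**Conclusion.** The point holds for participants and for the staff who prescribe and counsel: they can see the arm, under either description of the control. The participant-blinding statement in section H should not stand. Blinding of the principal investigator is unsupported as described, but it is not refuted.

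The consequence for the primary outcome is an exposure to bias, not a demonstrated one. As section E is written, self-report can decide the classification. The documents allow no estimate of the size or direction of any bias.

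Predictable allocation is a secondary and conditional point: up to 33.3% of assignments certain and up to 70.8% guessed correctly, if one enroller knows the block boundaries and all earlier allocations. The protocol prints the block size, and the visible regimens at one site can reveal the rest. Blinding and block size are both fixed in this protocol, so an unseen analysis plan would not resolve either.

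**What to change.** 1. In sections A and H, describe the trial as open to participants and treating staff. Retain a claim of blinding for the principal investigator only if the protocol also states how that role is kept apart from participants and treatment data.
2. State that cotinine and CO results, and abstinence status, are classified by ID number without the arm.
3. Replace the fixed block of four with randomly varied block sizes, keep the sizes out of the protocol, and have the list held by someone who does not enrol. Reword the phrase about each block's sequence at the same time.
4. Separately, reconcile the two control-arm descriptions in sections D and J.

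The cost is mainly wording and a regenerated list. The protocol names no laboratory or independent assessor, so the sponsor must settle who does the masked classification and whether that needs added effort. The trial would have to be reported as open-label, and arm balance during recruitment would be slightly looser.

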**I. Study tools:**

A semi-structured questionnaire will be developed to capture information about the participants' socio-demographic factors, smoking history, current smoking status, tobacco dependence score, medical history, follow-up of treatment, and stage of transtheoretical model during each visit. The participants will be assessed for carbon monoxide levels, body weight in kg during each visit and salivary cotinine test during the start and end of the follow-up. A pilot study will be conducted on ten participants to test the validity and feasibility of the tools. Processes of change questionnaire, fagerstorm test questionnaire, medication adherence rating scale, and clinician rating scale will be used in the study. Predictors of smoking cessation such as concern about own health, others' health due to passive smoking, smoking expenses, past quit attempts, etc will be measured. [16].

**J. Therapy protocol:**

| Activity                                                                 | Experimental Group                                                                                                                                                                                                                                                                                                                           | Control Group                                                                                                                                                                                                                                                                                            |
|--------------------------------------------------------------------------|----------------------------------------------------------------------------------------------------------------------------------------------------------------------------------------------------------------------------------------------------------------------------------------------------------------------------------------------|----------------------------------------------------------------------------------------------------------------------------------------------------------------------------------------------------------------------------------------------------------------------------------------------------------|
| Brief Advice (5 A's & 5 R's)                                             | 0-day, Month- 1, 3, 6, 9, 12                                                                                                                                                                                                                                                                                                                 | 0-day, Month- 1, 3, 6, 9, 12                                                                                                                                                                                                                                                                             |
| Nicotine Replacement Therapy for > 20 cigarettes per day                 | 
Nicotine Patch: Preloading for 4 weeks + 12 weeks post quit date
 
 
- 21 mg: 4 weeks before and after quit date
 
- 14 mg: Next 4 weeks
 
- 7 mg: Last 4 weeks
 
 
Nicotine chewing gums 4 mg for 12 weeks post quit date
(12/day on week 1.....1/day on week 12)
 | 
Nicotine Patch: 12 weeks post quit date
 
 
- 21 mg: 4 weeks after quit date
 
- 14 mg: Next 4 weeks
 
- 7 mg: Last 4 weeks
 
 
Nicotine chewing gums 4 mg for 12 weeks post quit date
(12/day on week 1.....1/day on week 12)
 |
| Nicotine Replacement Therapy for < 20 cigarettes per day                 | 
Nicotine Patch: Preloading for 4 weeks + 12 weeks post quit date
 
 
- 21 mg: 4 weeks before and after quit date
 
- 14 mg: Next 4 weeks
 
- 7 mg: Last 4 weeks
 
 
Nicotine chewing gums 2 mg for 12 weeks post quit date
(12/day on week 1.....1/day on week 12)
 | 
Nicotine Patch: 12 weeks post quit date
 
 
- 21 mg: 4 weeks after quit date
 
- 14 mg: Next 4 weeks
 
- 7 mg: Last 4 weeks
 
 
Nicotine chewing gums 2 mg for 12 weeks post quit date
(12/day on week 1.....1/day on week 12)
 |
| CO monitoring, Fagerstorm score, smoking frequency, medication adherence | 0-day, Month- 1, 3, 6, 9, 12                                                                                                                                                                                                                                                                                                                 | 0-day, Month- 1, 3, 6, 9, 12                                                                                                                                                                                                                                                                             |
| Health related quality of life                                           | 0-Day, 6 months, 12 months                                                                                                                                                                                                                                                                                                                   | 0-Day, 6 months, 12 months                                                                                                                                                                                                                                                                               |
| Saliva cotinine test                                                     | 0-day, Month- 3, 6, 12                                                                                                                                                                                                                                                                                                                       | 0-day, Month- 3, 6, 12                                                                                                                                                                                                                                                                                   |

**K.Statistical Analysis:** The collected information will be summarized by using frequency and percentage for qualitative data, mean and standard Deviation for quantitative data. To compare the outcome measures, quantitative before and after intervention, paired-t test will be used. If data is not following normal distribution, Wilcoxon Signed Rank test will be used. To compare qualitative outcomes, Chi-square test or Fischer exact test will be used. To compare the difference in outcome measures between two intervention groups, independent sample 't' test will be used. If data is not following normal distribution, Mann Whitney test will be used. The P value less than 0.05 will be considered as statistically significant.

**Results:** The study shall adopt the "Intention to Treat Analysis" mechanism. If the study has missing data more than 10% of the total sample size as expected during sample size calculation, Pattern-Mixture Model within a mixed-effects logistic regression model for longitudinal dichotomous data will be used. Because of the dichotomous outcome, logistic regression version of the mixed-effects model is applicable. The pattern-mixture effects for drug, time, data pattern and their interactions will be interpreted. Pattern mixture sensitivity analysis using SAS/STAT, missing data analysis will be done using R software, and survival analysis will be used to analyze the variation in smoking relapse over time related to the socio-demographics, smoking history, and treatment-related variables.

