**E. Primary Outcomes:**

The primary clinical outcome will be the binary smoking cessation; abstinence or non-abstinence assessed at 12 months from the starting point of intervention. Non-abstinence will be defined as self-reported smoking anytime during the intervention or follow up and a positive salivary cotinine test.

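### The only test named for comparing abstinence between arms is unadjusted, although baseline dependence and smoking frequency are collected; adjusting for them is a modest efficiency gain at no data cost

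*Protocol*

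**What the plan says.** - **Outcome (section E).** "The primary clinical outcome will be the binary smoking cessation; abstinence or non-abstinence assessed at 12 months from the starting point of intervention".
- **Test (section K).** "To compare qualitative outcomes, Chi-square test or Fischer exact test will be used". The other tests named there (paired and independent t tests, Wilcoxon, Mann-Whitney) are for quantitative data. By elimination, chi-square or Fisher is the test for abstinence. No covariate or stratum is named.
- **Randomisation (sections A and H).** The design is a "superiority trial with 1:1 allocation ratio", and "block randomization will be done to obtain the two groups using a computer-generated table". The blocks are of four, and no stratification factor is given.
- **Baseline data (section J).** The row "CO monitoring, Fagerstorm score, smoking frequency, medication adherence" is scheduled at day 0 and at later visits. The same table has separate treatment rows for more and for fewer than 20 cigarettes per day, in both arms.
- **Conditional model (Results paragraph after section K).** If missing data exceed 10%, a mixed-effects logistic pattern-mixture model is used. The terms named are drug, time, data pattern and their interactions. A survival analysis of relapse uses socio-demographics, smoking history and treatment-related variables.
- **Sample size (section G).** "6-month sustained abstinence was 47.5% for the intervention group and 27.5% for the control group", with "level of significance of 5%, power of 80% in the two-sided test", giving 91 per arm and then 100 per arm after allowance for 10% loss.

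**The concern.** The trial collects two natural candidates for baseline adjustment and makes predictors of cessation an objective. Neither the design nor any named between-arm analysis of abstinence uses these two variables. If they predict abstinence, leaving them out of the comparison costs some power. Section G leaves little to spare: 100 per arm less 10% loss is 90, one below the 91 required. The assumed rates are also for 6 months, while the primary outcome is at 12 months.

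Pre-specification matters as well. If covariates are not fixed in advance, the decision to adjust may be taken only after an imbalance has been seen.

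**Working it through.** **1. The plan's own figure.** Inputs from section G: p1 = 0.475, p0 = 0.275, two-sided 5%, power 80%. The mean rate is 0.375. The unadjusted two-proportion formula with pooled variance under the null is

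n = [1.960 × √(2 × 0.375 × 0.625) + 0.842 × √(0.475 × 0.525 + 0.275 × 0.725)]² / 0.20²

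= [1.342 + 0.564]² / 0.04 ≈ 90.8, rounded up to **91 per arm**. The stated figure reproduces, so sample size and named test agree.

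**2. Unadjusted power by number analysed per arm (same formula).**

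| n per arm | Power |
|---|---|
| 90 | 79.7% |
| 91 | 80.1% |
| 100 | 83.7% |
| 490 | above 99.99% |

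**3. Gain from adjustment.** The protocol gives no prognostic strength for dependence or smoking level, so the odds ratio per SD is an assumption. Each simulated trial had one standard normal baseline covariate, with marginal rates held at 47.5% and 27.5%. Unadjusted chi-square was compared with a logistic likelihood-ratio test adjusted for the covariate. There were 4,000 trials per row at 91 per arm, with simulation error of about √(0.8 × 0.2 / 4000) = 0.6 points per figure.

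| Assumed OR per SD | Unadjusted | Adjusted | Gain (points) |
|---|---|---|---|
| 1.0 | 80.9% | 80.4% | −0.5 |
| 1.3 | 82.2% | 82.7% | about +0.5 |
| 1.5 | 80.4% | 81.3% | +0.9 |
| 2.0 | 82.2% | 84.5% | about +2.3 |
| 2.5 | 82.2% | 87.5% | +5.3 |

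The marginal rates are fixed, so the spread in the unadjusted column is simulation noise.

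A separate set of 6,000 trials per setting at 90 per arm agrees. Unadjusted and adjusted power were 80.9% and 81.0% (OR 1.35), 80.5% and 81.9% (1.65), 80.4% and 82.6% (2.0), and 80.4% and 85.1% (2.46). The gains are 0.1, 1.4, 2.2 and 4.7 points.

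**4. Validity.** With both rates at 27.5% and 91 per arm, simulated type I error was 4.8% to 5.5% unadjusted and 4.9% to 5.8% adjusted. Neither shows inflation beyond simulation error.

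**5. Chance imbalance.** At 90 per arm the standard error of the between-arm difference in a standardised covariate is √(2/90) = 0.149 SD. At 37.5% overall abstinence and OR 1.35 to 2.5, an imbalance of that size moves the unadjusted risk difference by 1.0 to 2.7 points. The standard error of the risk difference itself is √[(0.475 × 0.525 + 0.275 × 0.725)/90] = 7.1 points. The share of variance is therefore (1.0/7.1)² = 0.02 to (2.7/7.1)² = 0.14, and it is already inside that standard error.

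**6. Which sample size applies.** Section G gives 100 per arm. Section C gives 490, and section H gives 245 blocks of four, which is 980 in total. The budget section's quantities and unit prices at 100 per arm come to:

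- patches: 100 × 120 × 8 + 100 × 90 × 8 = 168,000
- gums: 200 × 600 × 0.35 = 42,000
- cotinine kits: 200 × 4 × 8 = 6,400

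The total is 216,400 USD against 228,400 USD for materials and supplies. At 490 per arm the same items cost 4.9 × 216,400 ≈ 1.06 million USD, above the whole budget of 421,684 USD. The smaller trial is the more plausible reading, but the protocol does not settle it.

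**The case against.** The strongest reply is that nothing here is wrong. A chi-square test after 1:1 randomisation is valid, holds its type I error and matches the sample-size formula. Covariate lists are often left to a statistical analysis plan, which is not at hand. Section K is one generic paragraph that never mentions the primary outcome. All of this stands, and it limits the point to an improvement. The suggestion remains useful because the protocol does name a test, and names it without covariates.

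A reader might infer stronger things that the protocol does not support:

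- **That the baseline data go unused.** Smoking history enters the relapse survival analysis, predictors of cessation are an objective, and smoking level determines the treatment row. The gap is confined to the between-arm comparison of abstinence.
- **That chi-square is the only analysis of abstinence.** Above 10% missing data a mixed-effects logistic model is planned. It names no baseline covariate either, so the gap remains there.
- **That chance imbalance is a second harm beside lost power.** It is part of the standard error (step 5), and the test already allows for it. Counting both counts the same variance twice.
- **That dependence and cigarettes per day are established as strong predictors.** Section I names other predictors and ends the list openly. Section C excludes people smoking fewer than 10 cigarettes a day, which narrows the spread of that covariate. The strength is an assumption, and at the weak end the gain is nil.

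**Conclusion.** The point holds as a modest efficiency improvement. No stratification factor or baseline covariate is named for the comparison of abstinence, in the simple test or in the conditional mixed model. At about 90 per arm, adjustment would add roughly 0 to 5 points of power. This assumes a single covariate with an odds ratio per SD of 1.0 to 2.5 and the abstinence rates in section G. Only the top of that range approaches 5 points; at an odds ratio of 1.5 or below the gain is about one point or less. At 490 per arm there is essentially nothing to gain in power, so the unresolved conflict between 100 and 490 per arm is the larger problem and decides whether this point affects power at all.

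**What to change.** Before final data are seen, specify as the primary comparison a logistic regression of 12-month abstinence on arm, baseline Fagerström score and baseline cigarettes per day. Enter both covariates as continuous. Report the standardised (marginal) risk difference with its 95% CI, so that the result stays on the scale used for planning. Add the same two baseline covariates to the mixed-effects logistic pattern-mixture model; the 10% rule that triggers it can stay as written. Keep the chi-square or Fisher test as a supporting analysis.

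The cost is analysis wording in section K and the Results paragraph. Both variables are already scheduled at day 0, and randomisation need not change.
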